## Abstract

**Background:**

Older people have higher rates of hospital admission than the general population and higher rates of readmission due to complications and falls. During hospitalisation, older people experience significant functional decline which impairs their future independence and quality of life. Acute hospital services comprise the largest section of health expenditure in Australia and prevention or delay of disease is known to produce more effective use of services. Current models of discharge planning and follow-up care, however, do not address the need to prevent deconditioning or functional decline. This paper describes the protocol of a randomised controlled trial which aims to evaluate innovative transitional care strategies to reduce unplanned readmissions and improve functional status, independence, and psycho-social well-being of community-based older people at risk of readmission.

**Methods/Design:**

The study is a randomised controlled trial. Within 72 hours of hospital admission, a sample of older adults fitting the inclusion/exclusion criteria (aged 65 years and over, admitted with a medical diagnosis, able to walk independently for 3 meters, and at least one risk factor for readmission) are randomised into one of four groups: 1) the usual care control group, 2) the exercise and in-home/telephone follow-up intervention group, 3) the exercise only intervention group, or 4) the in-home/telephone follow-up only intervention group. The usual care control group receive usual discharge planning provided by the health service. In addition to usual care, the exercise and in-home/telephone follow-up intervention group receive an intervention consisting of a tailored exercise program, in-home visit and 24 week telephone follow-up by a gerontic nurse. The exercise only and in-home/telephone follow-up only intervention groups, in addition to usual care receive only the exercise or gerontic nurse components of the intervention respectively. Data collection is undertaken at baseline within 72 hours of hospital admission, 4 weeks following hospital discharge, 12 weeks following hospital discharge, and 24 weeks following hospital discharge. Outcome assessors are blinded to group allocation. Primary outcomes are emergency hospital readmissions and health service use, functional status, psychosocial well-being and cost effectiveness.

**Discussion:**

The acute hospital sector comprises the largest component of health care system expenditure in developed countries, and older adults are the most frequent consumers. There are few trials to demonstrate effective models of transitional care to prevent emergency readmissions, loss of functional ability and independence in this population following an acute hospital admission. This study aims to address that gap and provide information for future health service planning which meets client needs and lowers the use of acute care services.

**Trial Registration No:**

Australian & New Zealand Clinical Trials Registry ACTRN12608000202369

## Background

The ageing of the Australian population presents a significant challenge to the delivery of health services [1]. A significant proportion (13%) of people in Australia is now aged over 65 years [2], with almost one quarter of these older persons suffering from a severe or profound disability [3]. Maintaining functional ability and independence is thus becoming increasingly important to sustain or improve older people's quality of life and contain health care costs. Older people are found to have higher rates of hospital admission and length of stay than the general population. In 2008-09, approximately 3 million separations were recorded by public and private hospitals throughout Australia for older admitted patients (65 years and older), representing 37% of all separations [4]. These rates are comparable to other developed countries where persons aged 65 years and older account for approximately 38% [5] and 36% [6] of hospital admissions in the United Kingdom and United States, respectively.

During hospitalisation older people experience significant functional decline which results in loss of independence, decreased quality of life, and an increased rate of readmission [7-9]. Functional ability is closely tied to quality of life as it is essential for independence in the performance of activities of daily living (ADLs) (e.g., bathing, dressing, transferring, toileting, continence, and feeding) and instrumental activities of daily living (IADLs) (e.g., travelling, shopping, preparing meals, housework, and managing medications, the telephone, and money). One study found that of 1279 community-dwelling patients aged 70 years or over who were admitted to hospital for an acute medical illness, 32% were found to have a decreased ability to perform ADL functions on discharge compared with their pre-admission baseline, with the largest decline occurring in bathing and dressing [9]. At 3 months after discharge, 40% of the study population were found to have a new ADL and/or IADL disability, indicating that functional decline can be long-term. German et al. [10] therefore argue that quality of life can be increased if the rate of hospitalisations for acute episodes can be reduced or eliminated.

The successful move away from institutional-based care has resulted in higher numbers of older adults living at home, often cared for by relatives or spouses of a similar age [11]. Transitional care between hospital and home is required which effectively enables both the older person and their carer, if applicable, to manage at home. Discharge planning aims to improve patient outcomes and contain costs through an in-depth assessment and the development of an individualised plan for the patient prior to leaving hospital. Inadequate assessment of mental and physical status, social and health service support may result in a failure to recognise potential problems which contribute to readmissions. In a systematic review, Shepperd et al. [12] found evidence that discharge planning reduces readmission to hospital and hospital length of stay for older adults with a medical condition. A variety of strategies have been used to strengthen discharge planning, such as early screening, specialised geriatric programs, liaison nurses, and case management [13]. However, strategies are rarely evaluated directly, as outcomes are often assessed by systems measures such as length of hospital stay, rate of readmission and/or costs, rather than focusing on functional ability or psycho-social well-being and of the older person [13].

Evaluations have found readmissions to acute care facilities are decreased with in-home follow-up by nurses [13,14] and that exercise programs, in particular home-based programs, have shown promising results on the health outcomes of older adults [15].

Evidence surrounding case management models for older people, however, remains controversial [16,17]. Lowe and Kasap [18] describe a new model for reorganisation of geriatric and general medical services in a tertiary referral hospital. An iterative process of bed utilisation review, stakeholder consultation, and service remodelling was undertaken to improve bed management and resulted in a reduced length of stay, increased throughput and recurrent cost savings. However, limited work has been undertaken on the promotion of health behaviour change to improve the functional ability of older people at high risk of poor outcomes following discharge in order to improve the maintenance of independence and quality of life.

This research team previously completed a randomised controlled trial investigating the effectiveness of an innovative model of discharge planning and follow-up management of older adults at risk for hospital readmission [19]. The current trial extends this work to determine the effectiveness, as compared to that of receiving usual care, of interventions that 1) combine in-home and telephone follow-up management with hospital-to-home exercise strategies as outlined in the previous trial [19], 2) exercise strategies only intervention, and 3) an in-home and telephone follow-up only intervention. At the writing of this article (December 2010 to March 2011), ethics approval has been obtained and the interventions and data collection from the participants is underway.

### Trial aims

The overall aim of this trial is to evaluate the relative effectiveness of transitional care strategies commencing during hospitalisation for community-based high risk older adults on emergency readmissions and health service use, functional ability and quality of life outcomes. Specifically, the aims are to:

1. Conduct a randomised control trial to compare and evaluate transitional care interventions targeting older patients aged over 65 years who are at risk of hospital readmission after discharge;

2. Compare and evaluate innovative exercise and telephone follow-up interventions following discharge in comparison to usual care, on primary and secondary outcomes at 4 weeks, 12 weeks, and 24 weeks. Primary outcomes include emergency health service use (i.e. unplanned readmissions, time to first unplanned readmission, unplanned Emergency Department, General Practitioner and other health service use), and functional ability. Secondary outcomes include health-related quality of life, psychosocial well-being, and cost effectiveness; and

3. Apply the RE-AIM evaluation framework [20] which uses Reach, Effectiveness, Adoption, Implementation, and Maintenance to assist in understanding the various factors which impact upon the intervention becoming a routine part of the usual care provided by a health service.

## Methods/design

### Study design and setting

The study is a randomised controlled trial to evaluate the effectiveness of exercise-based and/or in-home telephone follow-up strategies for older patients at risk of hospital readmission. Participants are recruited from two tertiary metropolitan hospitals. After baseline data is collected, participants are randomly assigned to one of four groups, either 1) the usual care control group, 2) the exercise and in-home/telephone follow-up intervention group, 3) the exercise only intervention group, or 4) the in-home/telephone follow-up only intervention group.

The usual care control group receives usual discharge planning provided by the health service. The exercise only intervention group, in addition to usual care, receives an assessment by a physiotherapist to form the basis for an individually designed exercise plan aimed at improving functional ability. The program commences in-hospital and is followed up in-home at 6 weekly intervals for 24 weeks by an exercise physiologist. The exercise and in-home/telephone follow-up intervention group, in addition to usual care and the exercise intervention, receives an intervention from admission to 6 months post discharge including home visit/s following hospital discharge and regular telephone follow-up from a gerontology nurse for 6 months post-discharge. The in-home/telephone follow-up only group receives the in-home visits and telephone follow-up from the gerontology nurse as outlines above, with the omission of the exercise program. Participants in all groups complete assessments at baseline (within 72 hours of hospital admission), 4 weeks following hospital discharge, 12 weeks following hospital discharge and 24 weeks following hospital discharge.

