### Study outcomes

#### Primary outcomes

Primary outcomes include emergency health service use (i.e. unplanned readmissions, time to first unplanned readmission, unplanned Emergency Department, General Practitioner and other health service use), and functional ability (Instrumental Activities of Daily Living [23], Index of Activities of Daily Living [24], Walking Impairment Questionnaire [25]).

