#### Primary and secondary analysis

All data analyses will be conducted based on the principle of intention to treat [22]. Chi square, ANOVA, and Kruskal-Wallis tests will be used for bivariate analysis. For the primary outcomes of emergency health service use, Kaplan-Meier survival curves and log rank statistic will be used to compare intervention and control groups. A Cox proportional hazards regression model will be used to determine the effect of the interventions and adjust for any potential confounding variables. A general linear model approach will be used for multivariable repeated measures analysis of covariance for continuous outcome variables (e.g. measures of functional status, quality of life and psycho-social well-being) to investigate the differences over the four data collection points. Economic data will be collected to enable a comprehensive evaluation of the cost-effectiveness of the interventions when compared to that of usual care. Mean treatment costs differentials between control and intervention groups will be calculated. The patient level data will be used alongside other routinely available data to inform a decision analytic cost-effectiveness model.

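### The pre-randomisation ward score should be a covariate for the functional primary outcomes, not the first of four repeated outcome points

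*Protocol article*

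**What the plan says.** Under Study design and setting, the protocol article states: "Participants in all groups complete assessments at baseline (within 72 hours of hospital admission" and then at 4, 12 and 24 weeks after discharge. The Randomisation section places allocation after this baseline assessment. The Primary outcomes section lists "functional ability (Instrumental Activities of Daily Living [23], Index of Activities of Daily Living [24], Walking Impairment Questionnaire [25"] beside emergency health service use.

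Under Primary and secondary analysis, continuous outcomes, with functional status given as an example, go into a general linear model for repeated-measures analysis of covariance "to investigate the differences over the four data collection points". Four points can only mean baseline plus the three follow-up assessments.

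The Trial aims set a different comparison: the interventions "in comparison to usual care, on primary and secondary outcomes at 4 weeks, 12 weeks, and 24 weeks". Baseline is not among those times.

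The article gives no reference period (current or pre-admission) for the baseline functional items.

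**The concern.** A score taken before allocation cannot carry a treatment effect. Entered as an outcome level, it adds to the treatment comparison a time at which the groups differ only by chance. What follows depends on which term of the model is read:

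- A group effect averaged over all points is pulled towards zero.
- A group-by-time contrast against baseline becomes a difference in change scores, which is noisier than baseline adjustment.
- A plain group difference at one follow-up week leaves the baseline information unused.

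Interpretation is also at stake. The first point is taken on an acute ward and the other three after discharge. If the baseline items are scored on current ward status, change from baseline within a group includes recovery from the acute illness. It could not then be described as decline, or absence of decline, from function before admission. The Background describes functional loss in that way when it cites a cohort in which "32% were found to have a decreased ability to perform ADL functions on discharge compared with their pre-admission baseline".

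**Working it through.** **The plan's own figures.** The Sample size section is internally consistent (82 − 20 = 62 completers per group; 4 × 82 = 328) but rests on time to readmission. The article gives no power figure for the functional scales, so there is none to reproduce. The 62 per group is used below only to express precision.

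**Assumptions.** Equal SD (set to 1) at every point, and correlation r between baseline and a follow-up score. The article gives no r; 0.3 and 0.5 are illustrative. Step 2 further assumes the same r between every pair of points.

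**1. Pooled effect.** For a constant effect d at weeks 4, 12 and 24 and zero at baseline, the four-point average is (0 + d + d + d)/4 = 0.75d, a 25% dilution.

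**2. Precision of the pooled effect.** Averaging four points also changes the variance, so the 25% is not the whole cost.
- Variance of a four-point mean: (1 + 3r)/4.
- Variance of a three-point mean adjusted for baseline: (1 + 2r)/3 − r².
- Relative efficiency of the four-point analysis: 0.75² × [(1 + 2r)/3 − r²] ÷ [(1 + 3r)/4].
- r = 0.3: 0.5625 × 0.443 / 0.475 = 0.525. Then 62 per group inform like 62 × 0.525 ≈ 33.
- r = 0.5: 0.5625 × 0.417 / 0.625 = 0.375. Then 62 per group inform like 62 × 0.375 ≈ 23.

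**3. Single-week contrasts** (variance relative to the raw follow-up variance):

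| Contrast | Formula | r = 0.3 | r = 0.5 |
|---|---|---|---|
| Change from baseline | 2(1 − r) | 1.40 | 1.00 |
| Follow-up only, unadjusted | 1 | 1.00 | 1.00 |
| Follow-up adjusted for baseline | 1 − r² | 0.91 | 0.75 |

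The change score has 1.40/0.91 = 1.54 or 1.00/0.75 = 1.33 times the variance of the adjusted analysis. So 62 per group inform like about 40 (62/1.54) or 46 to 47 (62/1.33).

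With unequal SDs (baseline SD equal to s), the change-score variance is 1 + s² − 2rs. Its minimum, at s = r, is 1 − r². Apart from the small cost of estimating one slope, the change score therefore cannot beat adjustment at any s.

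**4. Bias.** A simulation used 62 per arm, a true effect of 0.5, 4,000 runs and assumed distributions in which acute illness shifts the ward score down by a varying amount:

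| Covariate | Mean estimate | SD of estimate | Power |
|---|---|---|---|
| Pre-admission score | 0.50 | 0.126 | 98% |
| Ward score | 0.50 | 0.145 | 93% |
| None | 0.50 | 0.181 | 79% |

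The estimate is unbiased throughout. Even a ward score is worth using as a covariate: under these assumptions it raises power from 79% to 93%.

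**The case against.** **The model may already be sound.** It is called an analysis of covariance, so baseline might be intended as a covariate and the four points be loose wording. A four-point model that constrains all groups to a common baseline mean would also recover the efficiency of adjustment. Both are possible. But the text counts baseline among the points compared and states no such constraint. The only adjustment rule it gives for baseline, under Descriptive analysis, is to control for differences that testing detects.

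**A stronger reading is tempting.** A reader might infer that the baseline records an acute trough, that the IADL and walking items cannot be performed on a ward, and that the trial therefore cannot show whether decline was prevented. The documents do not support this.

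- They fix when the baseline is taken, not the period the items ask about. Data come from patient questionnaires (Data quality assurance), which can ask about usual or pre-admission function. Item wording is commonly left to documents not shown here.
- The article's list of IADL tasks is "travelling, shopping, preparing meals, housework, and managing medications, the telephone, and money". Shopping and housework cannot be done on a ward, but telephone use can, and the impossibility of the others is itself a reason to expect a question about usual function.
- Patients unable to walk 3 metres independently are excluded (Exclusion criteria), and patients are approached when stable (Recruitment procedures).
- The pre-admission reference in the Background belongs to a cited cohort. Change from pre-admission function is not an endpoint of this trial. The Abstract's aim is to "reduce unplanned readmissions and improve functional status, independence, and psycho-social well-being", and less loss than under usual care can be shown by the randomised contrast.

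**Precision lost by not having a pre-admission rating** is likewise an assumption. Correlations of 0.3 against 0.6 give 0.91/0.64 = 1.42; 0.4 against 0.5 give 0.84/0.75 = 1.12; equal correlations give no loss. The 1.4-fold figure is not a finding about this trial.

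**Conclusion.** The point stands as one about the analysis. Treating the ward score as one of four outcome points dilutes a pooled constant effect by 25%. It makes change-from-baseline contrasts 1.33 to 1.54 times as variable as baseline-adjusted ones, for assumed correlations of 0.5 and 0.3 and equal SDs. The size depends on those correlations and on which model term is reported; the direction does not, unless a common baseline mean is imposed.

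The randomised comparison with usual care is not biased, and the stated sample size, which concerns readmission, is unaffected. Recovery from acute illness would enter within-group change if the items are scored on ward status, but it cancels on average from the difference between groups. Whether they are scored that way cannot be settled from the article, so that part is a clarification. The weight is moderate at most: the affected outcomes are primary, and the loss is avoidable before analysis.

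**What to change.** 1. In the analysis section, make weeks 4, 12 and 24 the outcome points for the IADL, ADL and walking scales, with the matching baseline score as a covariate whether or not a baseline difference is detected. Base conclusions on between-group differences at those weeks, as the Trial aims set out, and not on within-group change from the in-hospital score. This needs no new data and can be specified while the trial is running.
2. State the reference period of the baseline functional items. This costs one sentence.
3. If the questionnaires ask about current ward status, do not describe within-group change as decline from pre-admission function. A recalled pre-admission rating could be added to the baseline interview, before the randomisation envelope is opened, so that recall cannot differ by group. The Background says data collection is already underway, so this could cover only patients still to be enrolled. It would leave two forms of baseline and would rely on short-term recall. It is optional; the first change does not depend on it.

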### Study sample

#### Recruitment procedures

A hospital-based Research Assistant (RA) recruits participants from two tertiary referral hospitals in Australia. Participants are recruited from four acute medical wards and within 72 hours of admission to hospital. Each day (Monday to Friday), the RA checks the medical wards to determine if there have been any admissions within the last 24 hours (or if Monday morning, over the weekend). If there are any new admissions, the RA will check the patient's medical record to determine if they are eligible to participate in the trial as outlined in the study's inclusion and exclusion criteria (as defined below). If any new patients are eligible to participate, the RA will check that the patient's condition is stable and they are comfortable and, if so, will approach the patient, provide the patient information package, and explain the project. Consent will then be obtained if the patient is interested in participating in the project. If the patient provides consent to participate, the RA collects baseline data. Following collection of baseline data, the RA opens a sealed sequential randomisation envelope, which has been prepared previously by the Project Coordinator via a computerised randomised program, and the participant is randomised to one of the four groups: 1) the usual care control group; 2) the exercise and in-home/telephone follow-up intervention group; 3) the exercise only intervention group; or 4) the in-home/telephone follow-up only intervention group.

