#### Randomisation

Participants consenting to participate are randomly allocated into one of the four trial groups after the baseline assessment is completed. A randomisation master list was generated by the project coordinator via a computer-generated randomisation algorithm prior to commencement of recruitment.

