### Study conditions

#### Usual care control group (Group 1)

Patients who are allocated to the usual care control group receive routine discharge planning and rehabilitation advice as determined by the health service. If the hospital staff identify that in-home visits or rehabilitation services are required after discharge (e.g. community nursing visits), they are organised in the routine manner.

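### The research assistant who selects patients also opens the randomisation envelopes, so concealment depends on the recruiter alone; an independent release is available at little cost

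*Protocol article*

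**What the plan says.** All of the following is in the Protocol article.

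- **Recruitment procedures, screening.** For new admissions, "the RA will check the patient's medical record to determine if they are eligible to participate in the trial". Before any approach, "the RA will check that the patient's condition is stable and they are comfortable". Wards are checked on weekdays, and recruitment may take place up to 72 hours after admission.
- **Recruitment procedures, enrolment.** The RA approaches the patient and explains the project. Consent follows, worded in the passive. Then: "If the patient provides consent to participate, the RA collects baseline data".
- **Recruitment procedures, allocation.** After baseline, "the RA opens a sealed sequential randomisation envelope, which has been prepared previously by the Project Coordinator".
- **Randomisation.** "Participants consenting to participate are randomly allocated into one of the four trial groups after the baseline assessment is completed". The source of the sequence is also given: "A randomisation master list was generated by the project coordinator", before recruitment began.
- **Blinding.** The RA is described as blind at first because randomisation comes after baseline. Follow-up outcomes are collected off-site by a senior research assistant blind to group. Participants and intervention staff are not blind.
- **Study design and setting.** "Participants are recruited from two tertiary metropolitan hospitals".
- **Descriptive analysis.** Baseline differences that are detected will be controlled for. Hospital is not named.

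**The concern.** Concealment is strongest when the person who decides on entry cannot reach the next allocation until that decision is irrevocable. Here the person who decides on entry is also the person who breaks the seal. No second person or system is described as confirming that consent and baseline are complete before the allocation is revealed.

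At stake is the comparability of the four groups at entry. If an allocation became known early, the decision to approach a patient, or the order in which patients are approached, could depend on it, and every outcome would be affected. The RA also records the baseline data, so early knowledge could colour the covariates later used for adjustment.

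A smaller question is whether the groups will be balanced across the two hospitals, since the article mentions one master list and does not mention strata.

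**Working it through.** **1. Who controls each step.** No figure in the article bears on the allocation procedure, so this part is a comparison of the text.

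| Step | Who, according to the article |
|---|---|
| Generate the list, prepare envelopes | Project Coordinator |
| Screen records for eligibility | RA |
| Judge fitness to be approached | RA |
| Approach and explain | RA |
| Obtain consent | Not stated (passive), plausibly the RA |
| Collect baseline data | RA |
| Open the envelope | RA |
| Collect follow-up outcomes | Off-site senior research assistant, blind |

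The Project Coordinator appears only at the top of the chain. Every step from screening to opening belongs to the RA, apart from the unassigned wording on consent.

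**2. How much discretion there is.** The check on stability and comfort is a judgement. Weekday screening with a 72-hour window leaves some freedom over whom to approach first. A few risk factors in the Inclusion criteria (social support, degree of functional impairment) also need judgement. One risk factor is enough for entry, however, and others such as age are objective, so these matter only for some patients.

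**3. Whether later steps would repair selection.** Blinded follow-up protects the measurement of outcomes, not who was entered into which group. Adjustment for detected baseline differences reaches measured variables only. Neither repairs selection at entry.

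**4. Hospital balance, if the list is not stratified.** Inputs: 82 per arm (Sample size), two hospitals (Study design and setting), and an assumed split of recruitment between them, which the article does not give.

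SD of the difference in hospital share between two arms = sqrt(p × (1 − p) × 2/82).

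- p = 0.5: sqrt(0.25 × 2/82) = 0.078, or 7.8 percentage points; 1.96 × 0.078 = 0.153, a 95% range of about ±15 points.
- p = 0.7: sqrt(0.21 × 2/82) = 0.072, or 7.2 points; 1.96 × 0.072 = 0.141, about ±14 points.

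A simulation of 20,000 lists fixed at 82 per arm and not stratified agrees. With the 50:50 split, the absolute difference between two arms had a median of about 5 points and a 95th percentile of about 16. With 70:30, these were about 5 and 13.

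**The case against.** The strongest reply is that the article states real safeguards. The envelopes are sealed and sequential, someone other than the recruiter made them, and they are opened only after consent and baseline. An RA could learn an allocation early only by breaching the protocol. Opacity, tamper evidence, logging and custody are details that an article commonly leaves to the full protocol, so their absence is no fault. All of this stands. What remains is that the article does say who opens the envelope, and it is the recruiter.

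A reader might infer more than the text supports:

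- *That the RA has the next allocation in hand, or that envelopes lie open to inspection on the wards.* Where they are kept is not stated, and they are sealed.
- *That knowing past allocations lets the RA predict the next.* This would need a predictable restriction such as known blocks. None is described, and under simple randomisation the past predicts nothing.
- *That one series cannot be used in order at two hospitals.* The article describes a single RA recruiting from both, who could do so.
- *That each hospital sets its own usual care, so imbalance confounds the comparison.* Controls "receive routine discharge planning and rehabilitation advice as determined by the health service", in the singular, and no difference in practice between the hospitals is reported.
- *That the list is unstratified.* One master list does not exclude strata or separate series. Even if there are none, the comparison is unbiased in expectation, and the planned adjustment does not exclude hospital.

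Finally, changing allocation mid-trial has its own cost. The Background says that interventions and data collection are under way, and how much recruitment remains is unknown. That limits the benefit of the fix but does not remove the reason for it.

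**Conclusion.** The point holds in a limited form. Allocation is concealed by stated safeguards, but those safeguards, and the order of baseline before allocation, rest on the person who selects the patients. This is weaker than release by someone independent of recruitment, and such a person already exists in the trial. It is a risk in the design, not evidence of bias, and its size cannot be calculated from the document.

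The hospital question is secondary and conditional. The SD of 7.8 percentage points assumes no stratification and a 50:50 split. It describes chance imbalance, has not been translated into an effect on any outcome, and supports only a minor suggestion about the analysis.

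**What to change.** **Main change, for any remaining recruitment.** The Project Coordinator, who has no recruiting role in the text, holds the sequence. The RA reports participant ID, consent and completed baseline. The coordinator logs these with the time and only then releases the allocation. Any unopened envelopes in the RA's keeping go back to the coordinator.

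*Cost:* one call per participant and no extra staff. Allocation then depends on the coordinator being reachable on recruiting days. The procedure changes mid-trial, so the date of the change and the numbers allocated before and after it must be reported.

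**Secondary change.** State whether the list is stratified by hospital. If it is not, pre-specify hospital as a stratum in the log-rank and Cox analyses, instead of relying on whether a baseline difference happens to be detected. *Cost:* a line in the analysis plan and the recording of hospital for each participant.
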